#### Participant self-withdrawal

1) Participants who are unwilling or unable to continue with the clinical trial for any reason and request to withdraw from the trial are considered to have self-withdrawn;2) Participants who do not explicitly request to withdraw but do not receive treatment or participate in follow-up visits are considered lost to follow-up.

### Handling of dropout cases

Subjects who withdraw prematurely from the trial or are lost to follow-up will be contacted to complete a final assessment. Every effort will be made to collect efficacy and safety data for these subjects. Reasons for premature withdrawal will be documented in the case report form and trial conclusion form.

### Ineligibility criteria

(1) Incorrectly enrolled subjects who did not meet all inclusion criteria or met any exclusion criteria; (2) Subjects who met inclusion criteria but did not take the study medication or have no follow-up data; (3) Subjects who switched medications or added unspecified co-medications, especially those that could significantly impact assessment of efficacy and safety.

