### Exclusion criteria

(1) Secondary HUA caused by renal disease, hematological disorders, medication, tumor radiotherapy/chemotherapy, organ transplantation, or other reasons; (2) Use of allopurinol, febuxostat, benzbromarone, probenecid, or Chinese herbal medicine with uric acid-lowering effect within 4 weeks prior to enrollment; (3) History of stroke, transient ischemic attack, myocardial infarction, heart failure (NYHA class II-IV), or coronary artery surgery (such as angioplasty, stenting, or bypass surgery); (4) Abnormal liver function tests with aspartate aminotransferase (AST), alanine aminotransferase (ALT), or γ-glutamyltransferase (GGT) levels higher than 1.5 times the upper limit of normal at screening (Visit 1); (5) Abnormal renal function tests with serum creatinine (SCr) levels higher than 1.5 times the upper limit of normal at screening (Visit 1); (6) Co-existing malignant tumors or psychiatric disorders; (7) Known allergy or intolerance to any component of Kuiyuan chewing tablet or the investigational medicinal product excipients; (8) Known hypersensitivity or history of severe asthma exacerbated by nonsteroidal anti-inflammatory drugs (NSAIDs) or aspirin, or any component of NSAIDs or aspirin; (9) Use of oral corticosteroids for 10 or more consecutive days or use of intramuscular, subcutaneous, or intra-articular corticosteroids within 1 month prior to screening (Visit 1); (10) Co-existing autoimmune diseases; (11) Use or need for anticoagulants (such as aspirin, other salicylates, heparin, or warfarin) or antiplatelet agents (such as clopidogrel or ticlopidine); (12) Use or need for diuretics; (13) History of alcohol or drug abuse or daily use of analgesics for any reason; (14) Pregnancy, lactation, or planned pregnancy within 3 months after the last dose of investigational medicinal product; (15) Participation in other clinical studies within 3 months prior to screening (Visit 1); (16) Other conditions deemed unsuitable for this clinical study by the investigator.

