### Sample size calculation

According to the literature of Dalbeth N (25), Zhang X (26) et al., assuming that the effective rate of the experimental group is about 60% and the effective rate of the control group is about 30%, the sample size with a power of 0.8 was calculated to detect the difference between the two groups in terms of the effective rate, using the formula for comparing two sample proportions (27). The power of the test (1-β) was set at 0.8, and the significance level (Type I error rate) was set at 0.05 for a two-sided test. The sample size was estimated to be 53 per group, considering a dropout rate of 15%, resulting in a total of 126 participants, with 63 participants per group.

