#### Efficacy endpoints

##### Primary efficacy endpoint

The proportion of participants who maintained SUA levels <420 umol/L at week 12 (SUA levels were uniformly determined by uricase-peroxidase coupling assay, as described in Appendix 1).

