### Data analysis

The complete analysis set (FAS) and per protocol set (PPS) were used for efficacy evaluation analysis. The safety set (SS) was used for safety indicator analysis; since concomitant medications may affect efficacy and safety, the overall combination therapy was analyzed using the SS. General data was analyzed using the FAS and PPS. The last observation was carried forward for efficacy analysis for participants who withdrew prematurely. Dropouts with baseline data were included in efficacy analyses using the last observation carried forward. Excluded cases were not included in the efficacy statistical analysis, but those who received at least one treatment and had at least one safety record participated in the adverse reaction analysis.

To address potential confounding from lifestyle modifications, we will implement a three-pronged strategy to differentiate the specific effects of KYCT from those attributable to dietary control and health education. First, the double-blind placebo-controlled design ensures both groups receive identical lifestyle interventions, with KYCT administration being the sole therapeutic distinction between arms. Second, our primary analysis will employ analysis of covariance (ANCOVA) adjusting for key lifestyle covariates including physical activity levels (measured in MET-minutes/week) and daily purine intake (quantified through 24-hour dietary recalls). Third, sensitivity analyses will examine treatment effects in predefined adherent subgroups (≥80% protocol compliance for both medication intake and lifestyle recommendations) to assess outcome robustness against potential lifestyle adherence variations.

Furthermore, to address potential heterogeneity in treatment effects across subpopulations, three methodological safeguards have been incorporated: First, stratified randomization by baseline sUA tertiles (7.0-7.5, 7.6-8.5, >8.5 mg/dL) and sex ensures balanced subgroup distributions. Second, pre-specified Bayesian hierarchical models with regularizing priors [N(0,1)] will estimate subgroup effects while pooling information across multicenter clusters. Third, all subgroup comparisons will apply Benjamini-Hochberg FDR correction (<10%) within stratification categories, with results explicitly interpreted as exploratory hypotheses per CONSORT extension guidelines.

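### A participant who starts another urate-lowering drug can be removed from the efficacy analysis, or scored as failure or success, because no rule fixes the event as non-response

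*Protocol article*

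**What the plan says.** All references are to the protocol article.

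- **Ineligibility criteria, item 3**, covers "Subjects who switched medications or added unspecified co-medications, especially those that could significantly impact assessment of efficacy and safety". Urate-lowering drugs are not named, but with serum uric acid (SUA) as the endpoint they are the clearest example.
- **Data analysis** uses the full analysis set (FAS) and the per protocol set (PPS) for efficacy. It then states: "Excluded cases were not included in the efficacy statistical analysis". Any of them who were treated and have a safety record still count for adverse reactions.
- **Data analysis** treats dropouts differently: "Dropouts with baseline data were included in efficacy analyses using the last observation carried forward".
- **Handling of dropout cases** adds: "Subjects who withdraw prematurely from the trial or are lost to follow-up will be contacted to complete a final assessment". It does not say what happens to a value taken after another drug was started.
- **Primary efficacy endpoint** is "The proportion of participants who maintained SUA levels <420 umol/L at week 12", with no rule for participants who start another urate-lowering drug.
- **Exclusion criteria, item 2**, bars such drugs before entry: "Use of allopurinol, febuxostat, benzbromarone, probenecid, or Chinese herbal medicine with uric acid-lowering effect within 4 weeks prior to enrollment". Nothing says how a start during the trial is scored.

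The only other sentence on concomitant medication, in Data analysis, assigns an analysis of combination therapy to the safety set. It does not bear on the primary endpoint.

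**The concern.** Starting a urate-lowering drug during follow-up is likely to be a consequence of persistently high SUA, and so of failure on the primary endpoint. A rule that removes such participants after randomisation selects on outcome. It raises the response rate in every arm that has starters, and the FAS no longer compares the groups as randomised. The direction of the error depends on which arm has more starters: the difference shrinks if placebo has more, stays about the same if the shares are equal, and grows if Kuiyuan Chewing Tablet (KYCT) has more.

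The dropout route could distort the result more. If the final assessment is made on the new drug and is the value carried forward, a failure of the study treatment is recorded as a success. How a case is scored then depends on how the site or the data review classifies it.

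The event is plausible. Inclusion criteria require SUA above 480 umol/L after at least a month of diet. The guideline summarised in Background calls for drug treatment at 540 umol/L or more, or at 480 or more with certain comorbidities. SUA is measured at weeks 4, 8 and 12.

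**Working it through.** **1. Who are the excluded cases?** Data analysis gives no cross-reference. Three features of the text point to the list under Ineligibility criteria:
- Some excluded cases were treated and have safety records, so they are not screening failures.
- They are handled separately from dropouts.
- Item 1 of that list already covers people enrolled in breach of the Exclusion criteria, so that section is not a competing list.

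**2. What can happen to one starter?**

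| Classification | Handling | Primary endpoint |
|---|---|---|
| Ineligible, item 3 | Out of efficacy analysis | Removed |
| Dropout, last value before the new drug | LOCF | Failure, if that value is 420 or more |
| Dropout, final assessment on the new drug | LOCF | Success, if that value is <420 |

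**3. The plan's own figures.** Sample size calculation states: "The sample size was estimated to be 53 per group, considering a dropout rate of 15%, resulting in a total of 126 participants". Its inputs are 60% versus 30%, two-sided 0.05 and power 0.80. The dropout step reproduces: 53/(1 − 0.15) = 62.4, so 63 per group and 126 in total. The 53 does not: the usual two-proportion formula gives 42 per group, or 49 with continuity correction. That gap is conservative and does not affect this point. I use 63 per arm because dropouts are kept by LOCF.

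**4. Method.** Let f be the assumed share of an arm's non-responders who start a drug. The article gives no value for f.

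Power = Φ{(|p1 − p2| − 1.96·s0)/s1}, where
- s0 = √[p̄(1 − p̄)(1/n1 + 1/n2)], with p̄ the pooled rate;
- s1 = √[p1(1 − p1)/n1 + p2(1 − p2)/n2].

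With no starters: s0 = 0.0886, s1 = 0.0845, and power = Φ{(0.30 − 1.96 × 0.0886)/0.0845} = 0.932.

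**5. Exclusion route.** Placebo rate = 0.30/(1 − 0.70f), n = 63(1 − 0.70f). KYCT rate = 0.60/(1 − 0.40f), n = 63(1 − 0.40f). For example, with placebo f = 0.10 the rate is 0.30/0.93 = 0.323 and n = 58.6.

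| f KYCT | f placebo | KYCT | Placebo | Difference (points) | Power |
|---|---|---|---|---|---|
| 0 | 0.05 | 60.0% | 31.1% | 28.9 | 0.91 |
| 0 | 0.10 | 60.0% | 32.3% | 27.7 | 0.88 |
| 0 | 0.20 | 60.0% | 34.9% | 25.1 | 0.78 |
| 0.10 | 0.20 | 62.5% | 34.9% | 27.6 | 0.85 |
| 0.20 | 0.20 | 65.2% | 34.9% | 30.3 | 0.91 |
| 0.20 | 0.10 | 65.2% | 32.3% | 33.0 | 0.95 |

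With placebo starters only, power reaches 0.80 at f = 0.184, about 8 of the 44 expected placebo non-responders (63 × 0.70 = 44.1).

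**6. Dropout route, upper bound.** Every starter's carried value is on the new drug and <420, with n = 63 per arm. Placebo rate = 0.30 + 0.70f; KYCT rate = 0.60 + 0.40f.

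| f KYCT | f placebo | KYCT | Placebo | Difference (points) | Power |
|---|---|---|---|---|---|
| 0 | 0.10 | 60% | 37% | 23 | 0.74 |
| 0.10 | 0.20 | 64% | 44% | 20 | 0.62 |
| 0.20 | 0.20 | 68% | 44% | 24 | 0.78 |

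**7. Non-response rule.** If starters would not otherwise have reached <420, the rates stay at 60% versus 30% and power at 0.93 in every row. This follows from the assumption and is not separate evidence.

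**The case against.** The strongest reply has four parts.

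- **The link is inferred.** One section speaks of ineligibility and the other of excluded cases, and the article defines neither FAS nor PPS; set definitions often sit in a fuller document. The link is indeed an inference, but the article itself prints an exclusion from efficacy analysis without limiting it to the PPS. That is a stated rule, not a missing detail.
- **The dropout route takes several steps.** Starting another drug is not a listed withdrawal reason, and Data analysis does not say that the final assessment is the value carried forward. This stands: the route is conditional and its figures are an upper bound. It is still reachable, through the investigator's general discretion under Withdrawal criteria, or through Random allocation and blinding, where an unblinded participant is withdrawn and treated as a dropout.
- **Frequency is unknown, and modest exclusion does little harm.** This also stands. Participants accepted 12 weeks of possible placebo with any drug indication already present at entry. On the exclusion route, power stays above the planned 0.80 until about 18% of placebo non-responders are removed, and an excess of starters on placebo works against KYCT.
- **Non-response is one choice among several, and may come too late.** Other strategies can be defended, but the printed rules commit to none. Study design says recruitment ended in July 2023, and the article does not show whether the group codes are still closed.

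**Conclusion.** The concern holds. As printed, the rules take a participant who adds a urate-lowering drug out of the efficacy analysis altogether. They also leave open a second classification under which the same event may be scored as failure or success. The loss of the comparison as randomised does not depend on knowing the starter rate; the size of the effect does.

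Under the assumed shares, exclusion moves the difference to between 25.1 and 33.0 points, against 30 planned, with power from 0.78 to 0.95. In the dropout cases shown, the upper bound gives differences of 20 to 24 points and power of 0.62 to 0.78.

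These figures assume 63 analysed per arm before exclusions, true rates of 60% and 30%, and starters who would otherwise all be non-responders. Confidence is medium, because the reading of excluded cases is inferred and no starter rate is given. This should be corrected, but it does not by itself invalidate the design.

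**What to change.** Put one rule under Ineligibility criteria, Primary efficacy endpoint and Data analysis, settled before the group codes are opened:

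> *Anyone who begins a non-study urate-lowering drug before week 12, whether named in exclusion criterion 2 or not, remains in the full analysis set and counts as not having reached SUA <420 umol/L at week 12, whatever a later measurement shows.*

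Limit the item 3 exclusion to the PPS, and report the number of starters by arm.

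The cost is one sentence in three places and one count by arm, with no extra visits or participants. The drawback is that a few participants who might have reached <420 without the drug are scored as non-responders. That is acceptable when the question is whether the study treatment alone reaches the target. If the codes have already been opened, the rule can no longer be presented as prespecified; report it as a sensitivity analysis and say so.

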### Termination criteria

(1) Serious safety issues occurred during the trial; (2) Lack of clinically significant efficacy demonstrated for the study medicine during the trial; (3) Major errors in trial design or significant deviations from protocol that preclude efficacy evaluation; (4) Sponsor request for termination due to funding, management issues, or other reasons; (5) The China Food and Drug Administration orders termination of the trial.

### Random allocation and blinding

A double-blind, single-mimic approach was chosen because the placebo Tablet in the control group had the same appearance, specifications, size, and odor as the Kuiyuan chewable Tablet. All test drugs were provided by Beijing Qino Biotechnology Co., Ltd. and had uniform internal and external packaging.

A two-level blind design was adopted, with the first level corresponding to the group (such as Group A and Group B) for each case number and the second level corresponding to the treatment (test group and control group) for each group. The Institute of Basic Clinical Medicine of Traditional Chinese Medicine, China Academy of Chinese Medical Sciences, established the random coding table. The two-level blind bottoms were separately sealed, with two copies each, and stored at the Guang’anmen Hospital of the China Academy of Chinese Medical Sciences and Beijing Qino Biotechnology Co., Ltd., respectively.

Each coded investigational drug has a corresponding emergency letter, which contains a piece of paper indicating the type of drug that code is to be used in case of emergency unblinding. The emergency letter should be sealed and sent along with the investigational drug of the corresponding code to each clinical research center, where it should be kept by the center and not opened unless necessary. If a severe adverse event occurs or a subject needs to be rescued and it is necessary to know the treatment the subject received, the investigator may unblind the subject. Once unblinded, the subject will be withdrawn from the trial and treated as a dropout, and the reason for withdrawal should be recorded in the case report form by the investigator. All emergency letters will be collected along with the case report form at the end of the trial for the unblinding audit.

A two-step unblinding method was used. The data were locked after all case report forms were entered into the database, and the data underwent questioning, verification, and blinding audits. The investigator who kept the blind code then performed the first unblinding, revealing groups A and B. A biostatistician entered The data into the computer and linked it to the data file for statistical analysis. After the statistical analysis was completed, a second unblinding was performed to identify the treatment groups and the experimental and control groups.

### Sample size calculation

According to the literature of Dalbeth N (25), Zhang X (26) et al., assuming that the effective rate of the experimental group is about 60% and the effective rate of the control group is about 30%, the sample size with a power of 0.8 was calculated to detect the difference between the two groups in terms of the effective rate, using the formula for comparing two sample proportions (27). The power of the test (1-β) was set at 0.8, and the significance level (Type I error rate) was set at 0.05 for a two-sided test. The sample size was estimated to be 53 per group, considering a dropout rate of 15%, resulting in a total of 126 participants, with 63 participants per group.

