**Methods and analysis:**

This study is a multicenter, randomized, double-blind, parallel-controlled trial. HUA patients who meet the inclusion criteria will be randomly assigned in a 1:1 ratio to either (1) the control group (placebo of KYCT, specifications: 0.3g per tablet, 1.2g per dose, twice a day, taken with warm water 30 minutes after meals) or (2) the experimental group (KYCT, specifications: 0.3g per tablet, 1.2g per dose, twice a day, taken with warm water 30 minutes after meals). Both groups will receive dietary control, comorbidity prevention, and health education during the intervention period. The primary outcome will be the proportion of subjects with SUA levels <420 umol/L. Secondary outcomes will include the proportion of subjects with SUA levels <360 umol/L, the percentage change in SUA levels from baseline to each visit, the maximum percentage change in SUA levels from baseline to the third month, the number of gout attacks, changes in body measurements (weight, waist circumference, hip circumference, BMI), blood pressure, blood lipids, fasting blood glucose levels, and the proportion of subjects reporting gout attacks (cumulative up to each visit). Each group of patients will be assessed at baseline, as well as at the 4th, 8th, and 12th weeks.

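### The stated 80% power does not give 53 per group for 60% versus 30%; that size matches 90% power by the unpooled formula

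*Protocol article*

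**What the plan says.** The section "Sample size calculation" of the protocol article gives every input needed to repeat the calculation:

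- Response rates: "assuming that the effective rate of the experimental group is about 60" per cent, and "the effective rate of the control group is about 30" per cent.
- Power, given twice: "the sample size with a power of 0.8 was calculated to detect the difference between the two groups", and again "The power of the test (1-β) was set at 0.8".
- Test level: "the significance level (Type I error rate) was set at 0.05 for a two-sided test".
- Method: a formula for comparing two proportions, cited to a reference. The variant is not named.
- Result: "The sample size was estimated to be 53 per group, considering a dropout rate of 15%, resulting in a total of 126 participants", which is 63 per group.

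The abstract adds that patients "will be randomly assigned in a 1:1 ratio". No 90% power figure appears anywhere in the article.

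**The concern.** The inputs and the result stand in the same paragraph, so they should agree. For a difference as large as 60% versus 30%, 53 per group is more than 80% power requires.

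This paragraph is the only justification the article gives for enrolling 126 participants. If the stated power is not the power of the stated size, a reader cannot reproduce the number, and the results report is likely to repeat the wrong figure. The reader would also misjudge how sensitive the trial was if the result is null. The mismatch also hides spare power that could have paid for a more conservative choice, such as a stricter test or counting dropouts as failures.

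**Working it through.** **Inputs** (all from "Sample size calculation", except the 1:1 allocation, which is in the abstract): p1 = 0.60, p2 = 0.30, difference d = 0.30, two-sided alpha = 0.05 (z = 1.960), power 0.80 (z = 0.842), dropout 15%.

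Variance terms: p1(1−p1) + p2(1−p2) = 0.24 + 0.21 = 0.45. The mean rate is 0.45, so 2 × 0.45 × 0.55 = 0.495.

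**Step 1. Size per group at the stated 80% power**

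- Unpooled: n = (1.960 + 0.842)² × 0.45 / 0.09 = 39.2, so 40.
- Pooled under the null: n = (1.960 × √0.495 + 0.842 × √0.45)² / 0.09 = 41.97, so 42.
- Mean-rate variance throughout: n = (1.960 + 0.842)² × 0.495 / 0.09 = 43.2, so 44.
- Arcsine: 41.8, so 42.
- Continuity correction, n′ = (n/4) × [1 + √(1 + 4/(n·d))]²: from the unpooled n, 45.7, so 46; from the pooled n, 48.4, so 49.
- Fisher's exact test by enumeration: about 48 (power 0.800 at 48 per group).

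None gives 53. The largest, 49, is 4 per group short. A one-sided 5% level moves further away (31 to 40 per group).

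**Step 2. Size per group at 90% power** (z = 1.282)

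- Unpooled: n = (1.960 + 1.282)² × 0.45 / 0.09 = 52.5, so **53**, the stated figure.
- Pooled: 56. Arcsine: 56. Mean-rate variance: 58. Pooled with continuity correction: 63.

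**Step 3. Dropout**

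53 / (1 − 0.15) = 62.35, so 63 per group and 126 in total. This step is correct, and it shows that 53 is the evaluable number before the allowance for dropout.

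**Step 4. Power with 53 evaluable per group, 60% versus 30%, two-sided 0.05**

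| Test or approximation | Power |
|---|---|
| Unpooled normal | 0.902 |
| Pooled normal | 0.885 |
| Chi-square, exact enumeration | 0.878 |
| Pooled with continuity correction | 0.840 |
| Fisher's exact | 0.836 |

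The first line: √(0.45/53) = 0.0921; 0.30/0.0921 = 3.256; 3.256 − 1.960 = 1.296; the normal distribution function at 1.296 is 0.902.

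**Step 5. What 80% power would require in randomised patients**

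40/0.85 = 47.1, so 48 per group (96 in total). 49/0.85 = 57.6, so 58 per group (116 in total). Against 126, the paragraph as written supports 10 to 30 fewer participants than planned.

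**The case against.** The mismatch itself is not in dispute, but four points can be made against the diagnosis and its weight.

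- **90% is inferred.** The article gives 0.8 twice, which does not look like a single slip, and only the unpooled variant gives 53 at 90%. Changing the level instead also comes close at 80% power: two-sided 0.025 gives 51 (pooled) or 53 (mean-rate variance), though that contradicts the stated 0.05. This stands as a caution about the origin. It does not rescue 0.80.
- **The rates are given as approximate.** Assumed unrounded rates can reach 53 at 80% power: 60% versus 33% gives 52.4 (pooled), and 60% versus 32% gives 52.7 (unpooled with continuity correction). But the article states no such rates, and at the rates it does state the power of 53 per group is not 0.80.
- **Restating 0.90 could overstate power.** With a pooled or exact chi-square test it is 0.88, and with Fisher's test 0.84. This stands, which is why the restated figure must name its formula.
- **The consequence is small.** The trial has more power than claimed, no analysis changes, and the "Study design" section says recruitment has ended. This is true and limits the point to a correction of the text. The use of spare power for conservative dropout handling is an illustration; the plan itself carries the last observation forward.

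**Conclusion.** The concern holds. With the printed rates, level and allocation, no standard two-proportion method gives 53 per group at 80% power; they give 40 to 49. With 53 evaluable per group the design has power of 0.84 to 0.90, depending on the test, and 0.902 by the unpooled formula that reproduces 53. The later figures, 63 per group and 126 in total, follow correctly from 53.

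The conclusion takes the rates as exactly 60% and 30% and counts 53 evaluable participants per group. That the calculation was run at 90% is the most likely explanation, because it reproduces 53 within the stated rates and level, but it is not documented. The incompatibility of 0.80 with 53 does not depend on it. The trial is not underpowered under its own assumptions; the stated power is simply wrong for the stated size.

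**What to change.** In "Sample size calculation", change the power from 0.8 to 0.90 (β = 0.10) in both places and name the formula as the two-proportion comparison with unpooled variance. Keep 53 evaluable per group, 63 randomised per group and 126 in total. Before doing so, the sponsor should check its own calculation record. If that shows other inputs, such as unrounded rates or another formula, those should be printed instead so that 53 can be reproduced. It would help to add that power is about 0.88 with a chi-square test and 0.84 with Fisher's exact test.

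The cost is one corrected figure and a few words. Neither the sample size nor the analysis changes.
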